### 3.2 Secondary Endpoint:

- 1) The proportion of lupus low disease activity state (LLDAS) at week 96.
- 2) Short form-36 (SF-36) score of before and after treatment in two groups.
- 3) The proportion of adverse events of two groups in the follow-ups.
- 4) Changes in SLEDAI-2000 score.
- 5) Changes in prednisone dose.

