### **8.6 Secondary outcomes**

Secondary Endpoint including:

- 1) The proportion of lupus low disease activity state (LLDAS) at week 96.
- 2) Short form-36 (SF-36) score of before and after treatment in two groups.
- 3) The proportion of adverse events of two groups in the follow-ups.
- 4) Changes in SLEDAI-2000 score.
- 5) Changes in prednisone dose.

In descriptive statistics, data were expressed in the form of frequency (percentages) for categorical variables (proportion of LLDAS, proportion of adverse events (AEs)), medians (interquartile) or means  $\pm$  standard deviations (SD) for continuous variables (SF-36 score variation, SLEDAI-2000 score variation and prednisone dose).

In addition, t-tests were used to compare between-group differences in continuous variables after exploring the normality of data distribution using the Shapiro-Wilk test. Mann-Whitney U tests were used to compare continuous variables with a skewed distribution. Pearson Chi-square or Fisher's exact tests were used to compare between-group differences in categorical variables. All tests were performed two-sided at the significance level of 0.05.

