**Table 3 Outcomes of 96-week follow-ups.**

|  | Control group | MMF group | RR | P value |
|--|---------------|-----------|----|----------------|
|  |               |           |    |                |

|                                            | (n=)                  | (n=)                  |          |
|--------------------------------------------|-----------------------|-----------------------|----------|
|                                            | Mean (SD) or
N (%) | Mean (SD) or
N (%) | (95% CI) |
| Primary outcome, %                  |                       |                       |          |
| Proportion of severe flares                |                       |                       |          |
| Proportion of mild to moderate flares      |                       |                       |          |
| Severe flares, %                    |                       |                       |          |
| Lupus nephritis                            |                       |                       |          |
| Neuropsychiatric symptoms                  |                       |                       |          |
| Rash (prednisone dose > 0.5mg/kg/day)      |                       |                       |          |
| Pleurisy                                   |                       |                       |          |
| Thrombocytopenia (<60* 10  /L) |                       |                       |          |
| Pulmonary arterial hypertension            |                       |                       |          |
| Hemolytic anemia                           |                       |                       |          |
| Fever (prednisone dose > 0.5mg/kg/day)     |                       |                       |          |
| Henoch-Schonlein purpura                   |                       |                       |          |
| Moderate mitral insufficiency              |                       |                       |          |
| Arthritis (prednisone dose > 0.5mg/kg/day) |                       |                       |          |

**Mild to moderate flares,  
%**

Arthritis

Rash

Oral ulcer

Fever

Leukopenia  
( $1.5-4 \times 10^9/L$ )

Thrombocytopenia  
( $60-100 \times 10^9/L$ )

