**Secondary outcome, %**

Proportion of LLDAS,  
%

SLEDAI-2000 score at  
last visit

Prednisone at last visit  
(mg)

---

LLDAS: Lupus low disease activity state; SLEDAI: Systemic lupus erythematosus  
disease activity index;

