**Table 5. The comparison of SF-36 scores before and after treatment.**

SF-36: Short Form-36; PF: Physical functioning; BP: Bodily pain; MH: Mental

|                  |                     | PF | BP | MH | RP | VT | SF | GH | RE | HT | MCS | PCS |
|------------------|---------------------|----|----|----|----|----|----|----|----|----|-----|-----|
| Control
group | Before
treatment |    |    |    |    |    |    |    |    |    |     |     |
|                  | After
treatment  |    |    |    |    |    |    |    |    |    |     |     |
|                  | Change
in score  |    |    |    |    |    |    |    |    |    |     |     |
|                  | Before
treatment |    |    |    |    |    |    |    |    |    |     |     |
| MMF
group     | After
treatment  |    |    |    |    |    |    |    |    |    |     |     |
|                  | Change
in score  |    |    |    |    |    |    |    |    |    |     |     |

health; RP: Role physical; VT: Vitality; SF: Social functioning; GH: General health;  
RE: Role emotional; HT: Reported health transition; PCS: Physical component  
summary; MCS: Mental component summary.

**Table 6. The comparison of organ damage according to The Systemic Lupus International Collaborating Clinics (SLICC)/American College of Rheumatology (ACR) Damage Index (SDI) for SLE.**

|           | Control group (n=) N
(%)/ mean (SD) | MMF group (n=) N
(%)/mean (SD) | p value |
|-----------|----------------------------------------|-----------------------------------|----------------|
| SDI, %    |                                        |                                   |                |
| SDI, mean |                                        |                                   |                |

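### SF-36, SLEDAI-2000 and prednisone are compared without baseline adjustment, and Table 3 shows undefined last-visit levels for two endpoints defined as changes

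*Combined protocol and SAP*

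**What the plan says.** SAP 3.2 lists "Changes in prednisone dose" among the secondary endpoints, and SAP 8.6 repeats it next to "Changes in SLEDAI-2000 score". Neither has a time point; among the secondary endpoints only LLDAS is tied to week 96. SF-36 is to be compared before and after treatment, without saying which of the four later visits counts as after.

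SAP 8.6 gives the variables to be analysed as "SF-36 score variation, SLEDAI-2000 score variation and prednisone dose". The first two are changes, the third a level. For the tests, "t-tests were used to compare between-group differences in continuous variables after exploring the normality of data distribution using the Shapiro-Wilk test", and "Mann-Whitney U tests were used to compare continuous variables with a skewed distribution". Protocol 10.2 has the same rule. Neither section names a covariate, a repeated-measures model or an effect estimate for these outcomes.

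The Table 3 shell, titled "Outcomes of 96-week follow-ups", has rows for SLEDAI-2000 at last visit and "Prednisone at last visit". Its only estimate column is the relative risk with 95% CI. SF-36 is not in Table 3. It has its own shell, Table 5 ("The comparison of SF-36 scores before and after treatment"), with before, after and change rows. The Table 2 shells show mean SLEDAI-2000 by visit.

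The schedules in Protocol 7.6 and SAP 12 record SLEDAI-2000, SF-36 and medication at screening and at weeks 24, 48, 72 and 96.

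**The concern.** Three things are left open.

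- **Quantity compared.** The prednisone endpoint is a change in SAP 3.2, a level in SAP 8.6 and a last-visit level in Table 3. SLEDAI-2000 is a change in the text and a last-visit level in the table. The Shapiro-Wilk result then decides whether means or ranks are compared. An analyst could choose among these after seeing the data.
- **Precision.** The sample size was set for the flare rate, so the secondary outcomes get whatever precision 65 patients per group provides. Baseline SF-36 and SLEDAI-2000 enter only by subtraction, which uses them less efficiently than a covariate does.
- **Timing.** Last visit is not defined. If it means the last available visit, its timing depends on who leaves early, and that may differ between arms. Prednisone is tapered over time and raised at a severe flare, so the timing could affect the dose recorded.

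**Working it through.** **The plan's own figure.** The only calculated figure is for the primary endpoint. Exact enumeration of the two-sided unpooled Z test at 58 per group, 10% against 30%, gives power 0.8036, and alpha 0.0568 with both rates at 30%. 58/0.9 = 64.4, so 65 per group. All match. The documents give no SD, effect size or correlation for SF-36, SLEDAI-2000 or prednisone, so the correlation r below is an assumption.

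**Precision.** With one baseline and one follow-up value of equal SD, the relative variances are: final value 1; change score 2(1 − r); ANCOVA 1 − r². The ratio of ANCOVA to change score is (1 − r²)/[2(1 − r)] = (1 + r)/2. Power is for 58 per group, two-sided 0.05, with the effect (0.52 SD) set so that a final-value t-test has 80% power.

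| r (assumed) | Change score | ANCOVA | Cut against change | Cut against final value | Power, change | Power, ANCOVA |
|---|---|---|---|---|---|---|
| 0.3 | 1.40 | 0.91 | 35% | 9% | 65.8% | 83.6% |
| 0.5 | 1.00 | 0.75 | 25% | 25% | 80.0% | 89.9% |
| 0.7 | 0.60 | 0.51 | 15% | 49% | 95.1% | 97.5% |

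Because 2(1 − r) − (1 − r²) = (1 − r)², which is never negative, and 1 − r² never exceeds 1, ANCOVA is in large samples never less precise than either alternative. The size of the gain depends on r; its direction does not. SAP 8.6 specifies change for SF-36 and SLEDAI-2000, so the cut against change is the relevant column for them.

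**Prednisone.** Everyone starts at 0.5 mg/kg/day. Per kg, the baseline is nearly constant and adjustment gains almost nothing. In mg, the baseline is mainly a measure of body weight, and its correlation with the later dose is unknown. The percentages in the table do not carry over.

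**Pretest.** Over 10,000 simulated trials per distribution with no true difference, the two-stage procedure had type I error 0.0506 (normal), 0.0479 (gamma), 0.0499 (log-normal) and 0.0518 (discrete, SLEDAI-like). The error rate is sound; what is not fixed in advance is the quantity compared.

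**Timing.** For assumed weights of 40 to 100 kg, the written taper (four weeks at the starting dose, 5 mg steps every two weeks to 20 mg, then 5 mg monthly) reaches 0.2 mg/kg/day or less by about weeks 12 to 16. That is before the first follow-up visit at week 24. As an illustration, assume 60 kg, a mean of 6 mg at week 96, early exits of 10% in one arm and 20% in the other, and last visits spread evenly over weeks 24, 48 and 72:

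- Doses of 12, 11 and 10 mg (mean 11): 0.9×6 + 0.1×11 = 6.5 and 0.8×6 + 0.2×11 = 7.0, a shift of 0.5 mg/day.
- Doses of 9, 8 and 7 mg (mean 8): 6.2 and 6.4, a shift of 0.2 mg/day.
- If the 30 mg starting dose can also count as a last visit, the early-exit means become 15.75 and 13.5 mg, and the shifts about 1.0 and 0.75 mg/day.

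**Follow-up after severe flare.** Protocol 7.1.1 and 7.1.2 treat a severe flare as the end of the trial for that patient. SAP 4, note 1, keeps such patients under follow-up to the end. Protocol 8.1, item 1, contains both statements. SAP 8.5 says nothing is collected after loss to follow-up. Under the first reading, a severe-flare patient's last value may be taken at the flare, alongside the prednisone increase that Protocol 7.1.1 describes.

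**The case against.** **The plan does use baseline.** True for SF-36 and SLEDAI-2000: SAP 8.6 analyses variation, and Table 5 has a change row. A reader might infer that baseline and interim values go unused; the documents do not support that. The gap is narrower: no baseline covariate and no longitudinal model.

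**Last visit may simply mean week 96.** Table 3 is titled as 96-week outcomes, and week 96 is the last scheduled visit. This is a fair reading, and carrying values forward is stated nowhere. But the term is undefined, data stop at loss to follow-up, and the severe-flare passages conflict, so the other reading stays open.

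**Early leavers look worse on prednisone.** This is a possible inference, not one the documents establish. It needs last visit to mean last available visit, and on the written schedule most of the taper is over before week 24. What remains is physician-led tapering, a final step with no timetable, and doses taken at or after a flare.

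**The pretest does no harm to type I error.** Agreed.

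**A rank test suits SLEDAI-2000, which is discrete, and prednisone, which comes in 5 mg tablets.** This is a reason to keep Mann-Whitney as a sensitivity analysis, not to leave the main analysis to a pretest.

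**An empty relative-risk cell on a continuous row is ordinary.** It is, but no other column or text then supplies an estimate with an interval for these outcomes.

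**Conclusion.** The point holds as an efficiency and definition problem in the secondary analyses. For SF-36 and SLEDAI-2000, the planned change-score comparison has more variance than a baseline-adjusted one: adjustment would remove 35%, 25% or 15% of it at assumed correlations of 0.3, 0.5 or 0.7. For prednisone the gain is uncertain. Table 3's last-visit levels do not match the change endpoints for SLEDAI-2000 and prednisone, whatever last visit means. The mixing of follow-up times is conditional on its meaning last available visit; under the assumed doses the shift is 0.2 to 0.5 mg/day, or about 0.75 to 1.0 if starting doses are carried.

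The documents do not support three wider conclusions: that the last-visit problem covers SF-36, which is not in Table 3; that the Shapiro-Wilk step inflates false positives; or that the trial needs more patients, since its size rests on the flare rate alone.

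**What to change.** - In SAP 3.2 and 8.6, set week 96 as the time point for SF-36, SLEDAI-2000 and prednisone.
- Analyse the SF-36 summary scores and SLEDAI-2000 with a baseline-adjusted model: ANCOVA at week 96, or a mixed model over weeks 24, 48, 72 and 96 with baseline, arm, visit and arm-by-visit. Analyse prednisone per kg, or in mg adjusted for starting dose.
- Report the adjusted week-96 mean difference with its 95% CI, and state the missing-data rule.
- Replace the Shapiro-Wilk switch with this model and keep Mann-Whitney as a sensitivity analysis.
- Relabel the two Table 3 rows as week 96 and add a mean-difference column.
- Reconcile Protocol 7.1.1, 7.1.2 and 8.1 with SAP 4 on follow-up after severe flare.

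The cost is SAP wording, a table shell, reconciliation of the protocol text and slightly more modelling. No new data are needed, and the primary endpoint and sample size do not change.

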### 8.7 Other variables

In our trial, changes in serological markers, including anti-dsDNA antibody, immunoglobulin G (IgG), erythrocyte sedimentation rate (ESR), and C-Reactive Protein (CRP) were also assessed in the two groups.

The Systemic Lupus International Collaborating Clinics (SLICC)/American College of Rheumatology (ACR) Damage Index (SDI) was also compared in the two groups. Statistical analysis methods will be used appropriately for those variables.

### 9. Flow chart

Flowchart : see Figure 1.

### 10. Statistical software

The statistical analyses were performed using SPSS Statistics (version 23.0), GraphPad Prism (version 8.0), and R software (version 4.0.0). Figures will be plotted using GraphPad Prism (version 8.0) and R software (version 4.0.0).

### 12. Study content schedule

| content \ time                | Screening period | Follow-up period |         |         |         |
|-------------------------------|------------------|------------------|---------|---------|---------|
|                               | Screening day    | Week 24          | Week 48 | Week 72 | Week 96 |
| Informed consent form         | √                |                  |         |         |         |
| Inclusion/Exclusion Criterias | √                |                  |         |         |         |
| Physical examination          | √                | √                | √       | √       | √       |
| SLEDAI-2000 Index             | √                | √                | √       | √       | √       |
| Blood routine examination     | √                | √                | √       | √       | √       |
| Urine routine examination     | √                | √                | √       | √       | √       |

|                     |   |   |   |   |   |
|---------------------|---|---|---|---|---|
| ALT&AST             | ✓ | ✓ | ✓ | ✓ | ✓ |
| Scr                 | ✓ | ✓ | ✓ | ✓ | ✓ |
| ESR & CRP           | ✓ | ✓ | ✓ | ✓ | ✓ |
| Complement 3 & 4    | ✓ | ✓ | ✓ | ✓ | ✓ |
| Anti-dsDNA antibody | ✓ | ✓ | ✓ | ✓ | ✓ |
| immunoglobulin G    | ✓ | ✓ | ✓ | ✓ | ✓ |
| SF-36 score         | ✓ | ✓ | ✓ | ✓ | ✓ |
| Medication          | ✓ | ✓ | ✓ | ✓ | ✓ |
| Adverse events      | ✓ | ✓ | ✓ | ✓ | ✓ |

### **13. Ethics**

The study was approved by the Institutional Research Ethics Committee of Ruijin Hospital (ID: 2018-120) and the local authorized ethics committee of the other two clinical centers. All patients provided written informed consent.

### **14. Adverse events disposition**

Adverse events will be recorded during the follow-ups. Proper treatment would be given to deal with the adverse events.

### **15. Tables and figures**

## CONSORT Flow Diagram

[figure not shown]

**Figure 1 : Flowchart**

**Table 1 Baseline characteristics**

| Control group (n=)                | MMF group (n=)                     |
|-----------------------------------|------------------------------------|
| Median(quartile25%,75% ) or N (%) | Median(quartile25%,75 % ) or N (%) |

---

Age(years)

Female, N (%)

Disease

duration(months)

SLEDAI-2000 score

System involvement

Arthritis, N (%)

Rash, N (%)

Fever, N (%)

Alopecia, N (%)

Oral ulcer, N (%)

Leukopenia, N (%)

Thrombocytopenia, N  
(%)

Laboratory results

Anti-dsDNA antibody  
(IU/mL)

Low C3 level, N (%)

Low C4 level, N (%)

WBC (\*10^9/L)

Hemoglobin (mg/L)

Platelet (\*10^9/L)

ESR (mm/h)

CRP (mg/L)

---

SLEDAI: Systemic lupus erythematosus disease activity index; ESR: Erythrocyte sedimentation rate; CRP: C-Reactive Protein; WBC: White blood cell; MMF: Mycophenolate mofetil

**Table 2 and followings: MMF efficacy versus Control at visit xx**

|                                 | Control group (n=) | MMF group (n=) |
|---------------------------------|--------------------|----------------|
| SLEDAI-2000 Index, mean         |                    |                |
| Blood routine examination, mean |                    |                |
| Urine routine examination, mean |                    |                |
| ALT&AST, mean                   |                    |                |
| Scr, mean                       |                    |                |
| ESR, mean                       |                    |                |
| CRP, mean                       |                    |                |
| Complement 3 & 4, mean          |                    |                |
| Anti-dsDNA antibody, mean       |                    |                |
| Immunoglobulin G, mean          |                    |                |

SLEDAI: Systemic lupus erythematosus disease activity index; ALT: Alanine aminotransferase; AST:Aspartate aminotransferase; Scr: Serum creatinine; ESR: Erythrocyte sedimentation rate; CRP: C-Reactive Protein; MMF: Mycophenolate mofetil

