### **2.4 Risk/Benefit Assessment**

#### **2.4.1 Potential risks**

Currently, mycophenolate mofetil and glucocorticoids are used as first-line drugs in systemic lupus erythematosus. The research has no psychological harm, no financial loss and no legal harm to the patients. No pain and bodily harm. During treatment, patients may develop infection due to the use of glucocorticoids and immunosuppressants, as well as gastrointestinal reactions and blood counts that may be influenced by mycophenolate mofetil.

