## **9.3 Adverse events and serious adverse events**

### **9.3.1 Adverse Event (AE) Definition**

According to ICH-GCP definition

An adverse medical event that occurs in a patient or clinical trial subjects following the use of a drug, but for which there is not necessarily a causal relationship between this medical event and treatment. Thus, an adverse event may be any adverse and unintended sign (including abnormal laboratory findings), symptom, or disease temporally associated with the use of a (study) drug,

regardless of whether it is related to the (study) drug. Currently, mycophenolate mofetil and glucocorticoids are used as first-line drugs in systemic lupus erythematosus. Infection could be considered as the most common AE of both glucocorticoids and immunosuppressants.

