#### **9.3.4 Timing, frequency, follow-up, and regression of adverse event assessments**

The nature of the adverse event was determined by combining the definitions of AE and SAE from the ICH-GCP and GCP. All AEs including local and systemic reactions should be collected using a case report form (CRF) that collects information including description of the event, time of occurrence, physician's assessment of severity, relationship to the investigational product, and time to resolution/stabilization of the event. All AEs should be given adequate resolution. At each study follow-up visit, the investigator will ask about AEs/SAEs that have occurred since the

last follow-up visit, and the AE/SAE will be followed until resolved or stabilized.

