## **10.3 Security Analysis**

AEs are coded and calculated and may be expressed using severity, frequency, and association with the intervention. Adverse events leading to discontinuation of the research intervention and serious AEs resulting from treatment should be listed individually.

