### **3. Study outcomes**

#### **3.1 Primary Endpoint:**

The primary outcome was the proportion of patients who have flares (mild to moderate flares and severe flares) defined by modified SELENA-SLEDAI Flare Index (SFI)  at 96 weeks of follow-up.

The definition of mild to moderate flare is the fulfillment of one or more following items:

- 1) variation of SELENA-SLEDAI score  $\geq 3$  (but  $< 12$ );
- 2) new or worsening rashes, cutaneous vasculitis, nasopharyngeal ulcers, serositis, arthritis or fever caused by lupus;
- 3) increase in the dose of prednisone, but less than 0.5mg/kg/day;
- 4) increase of nonsteroidal anti-inflammatory drugs or HCQ;
- 5) Physician's Global Assessment (PGA) (0-3 scale)  $\geq 1$ .

Severe flare is defined as the fulfillment of one or more of the following items:

- 1) change in SELENA-SLEDAI score of more than 12;

- 2) new or worsening central nervous system involvement, vasculitis, nephritis, myositis, thrombocytopenia (platelet  $<60 \times 10^9/L$ ) or haemolytic anaemia (haemoglobin  $<70g/L$  or decrease in haemoglobin level  $>30g/L$ );
- 3) increased usage of prednisone (doubled in dosage or more than 0.5mg/kg/day);
- 4) added cyclophosphamide, azathioprine, methotrexate, mycophenolate mofetil or hospitalization because of lupus activity;
- 5) PGA  $>2.5$ .

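### The SAP table shells give no labelled per-arm count of patients with low blood counts as a harm, although the protocol names blood counts as an MMF risk

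*Combined protocol and SAP*

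**What the plan says.** Protocol 2.4.1 lists infection from glucocorticoids and immunosuppressants, and then "gastrointestinal reactions and blood counts that may be influenced by mycophenolate mofetil". Blood counts, ALT/AST and serum creatinine are measured at screening and at weeks 24, 48, 72 and 96 (Protocol 7.6; SAP 12).

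The shells in SAP 15 treat low counts as follows:

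- **Table 1 (baseline):** leukopenia and thrombocytopenia as N (%).
- **Table 2 (each visit):** headed "Table 2 and followings: MMF efficacy versus Control at visit xx". The haematology row is "Blood routine examination, mean", and ALT/AST and creatinine have the same form. No SD, N (%), grade or threshold appears.
- **Table 3 (outcomes):** leukopenia 1.5-4 and platelets 60-100 x10^9/L sit under mild to moderate flares. Platelets below 60 and haemolytic anaemia sit under severe flares.
- **Table 4 (adverse events):** total AEs, infection with six types, gastrointestinal event, bone fracture, osteonecrosis of the femoral head, and other events.

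On the adverse event side, Protocol 9.3.1 lets an abnormal laboratory result count as an adverse event, 9.3.4 has all adverse events recorded on the case report form, and 9.3.3.1 grades them by CTCAE 5.0. Protocol 10.3 says that adverse events are coded, allows them to be summarised by severity, frequency and relation to treatment, and adds: "Adverse events leading to discontinuation of the research intervention and serious AEs resulting from treatment should be listed individually". Protocol 8.1 includes ALT/AST above 2 x ULN and creatinine clearance below 60 ml/min among its discontinuation situations.

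**The concern.** Of the three risks that the protocol names, two have a labelled row in the safety table and the third does not. The count format used for leukopenia and thrombocytopenia at baseline is dropped once treatment starts, except where a low count is presented as a flare.

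The trial tests adding MMF early in patients without major organ involvement. A reader weighing that choice needs to set the number with clinically low counts on each arm against the flares avoided. From the shells as drawn, that reader would have an arm mean, a flare-labelled subset and an undivided residual row.

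**Working it through.** **1. Where a post-baseline low count could appear.** This point has no plan figure to reproduce, so the check is a reading of every shell row.

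| Shell | Haematology content after baseline | Labelled per-arm count as harm? |
|---|---|---|
| Table 2 | arm mean at each visit | No |
| Table 3 | four rows: leukopenia 1.5-4, platelets 60-100, platelets <60, haemolytic anaemia | No; all four are flare types |
| Table 4 | none by name; could fall in total AEs or other events | No |
| Tables 5 and 6 | none | No |

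Table 3 is incomplete as a substitute. Its leukopenia row stops at 1.5 x10^9/L, so the deepest falls have no row in any shell. SAP 3.1 names no white cell item in either flare definition, so an isolated low white cell count need not reach Table 3 unless another item is met, such as a score change or a prednisone increase.

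**2. What an arm mean can show.** The only input from the plan is n = 65 per arm, from 58/(1 - 0.10) = 64.4, rounded up. The plan gives no white cell SD and no size of fall. Assumed: SD 1.5 to 2.5 and falls of 2 to 4, all in x10^9/L.

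Shift in the arm mean if 3 of 65 patients fall = (3/65) x fall:
- fall 2: 0.09
- fall 3: 0.14
- fall 4: 0.18

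95% half-width for the difference in means = 1.96 x SD x sqrt(2/65):
- SD 1.5: 0.52
- SD 2.5: 0.86

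Patients who must fall before the mean difference equals its own half-width, k = half-width x 65 / fall, rounded up:
- fall 3, SD 1.5: 0.516 x 65/3 = 11.2, so 12 of 65 (18%)
- fall 3, SD 2.5: 0.860 x 65/3 = 18.6, so 19 of 65 (29%)
- fall 4, SD 1.5: 8.4, so 9 of 65 (14%)
- fall 2, SD 2.5: 27.9, so 28 of 65 (43%)

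**3. What a count row shows for the same three patients.** 3/65 = 4.6% (Clopper-Pearson 95% CI 1.0 to 12.9) against 0/65 = 0% (0 to 5.5). As a comparison it is weak: Fisher exact p = 0.24 for 3 v 0. The exact power of a two-sided 0.05 Fisher test is 0.06 for 5% v 1% and 0.46 for 10% v 1%. The row's value is descriptive.

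**The case against.** The strongest reply is that the safety analysis already reaches these events. Laboratory abnormalities can be adverse events, they are graded by CTCAE 5.0, and 10.3 has them coded and allows frequency and severity summaries. Coding gives each event a term, and a frequency by term is a labelled count. Blank shells do not forbid itemising the residual row in Table 4. This largely stands. It rules out the stronger reading that cytopenias would go uncollected or could not be reported. What it leaves is a permission rather than a commitment. The individual listing covers only adverse events that led to discontinuation and serious ones attributed to treatment, so a moderate leukopenia managed on continued MMF falls outside it. The plan also sets no value at which a laboratory result becomes an adverse event, so the count depends on who records it.

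A reader might also infer that raised liver enzymes or creatinine belong to the named risk. They do not: 2.4.1 mentions neither. At the limits in 8.1 they are discontinuation situations, so cases that are recorded as adverse events and lead to stopping would be listed individually under 10.3. The liver and renal gap is therefore smaller.

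A reader might go on to infer that the flare endpoint is biased, because the severe-flare item "new or worsening central nervous system involvement, vasculitis, nephritis, myositis, thrombocytopenia" carries a platelet limit of 60 x10^9/L and states no lupus cause. That is a question of endpoint attribution. A table row neither tests nor repairs it, so it adds no weight here. The efficacy heading on Table 2 is cosmetic.

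Finally, three outliers barely move any mean of 65, and every fall and SD in the illustration is assumed. That is fair. The arithmetic shows why means are the wrong summary for a rare harm, and does not predict how many patients will be affected.

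**Conclusion.** The point holds as a low-severity reporting gap. The protocol names an MMF effect on blood counts, and no SAP shell commits to a labelled number of affected patients per arm as a harm. Table 3 covers part of the range, as flares only, with nothing for white cells below 1.5 x10^9/L.

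Under the assumed SDs and falls, somewhere between 9 and 28 of 65 patients on one arm would have to be affected before a difference in means reached its own 95% half-width, whereas a count row displays three. The size rests on those assumptions; the absence of the row rests on the shells alone. No estimate, test or conclusion on flares changes.

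**What to change.** Add to Table 4, by arm, N (%) with 95% CI for the worst post-baseline CTCAE 5.0 grade of leukopenia, anaemia and thrombocytopenia, each with shift from baseline grade. Count every case regardless of attribution, and footnote how many were also scored as flares in Table 3. Present the rows descriptively, without tests.

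As a secondary addition, and not as a named risk, add N (%) with ALT or AST above 2 x ULN and with creatinine clearance below 60 ml/min, because 8.1 already uses those limits. State the clearance formula, since the visit schedules list serum creatinine only.

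The cost is a few table rows and some code; no new data are needed and no flare scoring changes. The downsides are:

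- Lupus cytopenias are mixed in, because entry allows white cells 1.5-4, haemoglobin 90-120 g/L and platelets 60-100. The shift from baseline is there to help separate them.
- Some patients will appear both here and in the flare counts.
- Power to compare arms is low.
- Transient falls between the 24-week visits are still missed.
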